### Assessments

2.4.

#### Global functioning

2.4.1.

ο Global Assessment of Functioning (GAF):

In our study, the GAF is used to evaluate subjectively the social and psychological functioning of the participants and the impact of psychiatric illness on an individual’s life and daily functional skills and abilities. Scores range from 100 (“extremely high functioning”) to 1 (“severely impaired”). It differentiates 10 levels of psychosocial functioning (59). A higher score reflects higher functioning in everyday life based on scored criteria.

ο Behavior Rating Inventory of Executive Function (BRIEF):

Executive function behaviors in the school and home environments will be assessed using the BRIEF. This questionnaire is elaborated for parents and teachers of school-age children. It includes eight clinical scales (Behavioral regulation scales and Metacognition scales) and two validity scales (Inconsistency and Negativity) that give the clinician a well-rounded picture of the behavior of the adolescent being rated. The Global Executive Composite score takes into account all of the clinical scales and represents the adolescent’s overall executive function (60).

#### Social cognition

2.4.2.

We will evaluate social cognition using the Tunisian Social Situations Instrument (TSSI) (61) and the Facial Emotions Tunisian Test for Children (FETTC) (62). These tasks are Tunisian validated and computerized tests. They consist on downloadable applications on Android (more convenient and more attractive for patients).

ο Tunisian Social Situations Instrument (TSSI) (61):

It is a comprehension test composed of 10 social situations evaluating the attribution of intentions and epistemic and affective mental states to the protagonists of the social stories. Each situation includes a text written in the Tunisian Arabic dialect illustrated by one or more pictures with a synchronized reading of the text and questions. The reading of the texts and the questions is done automatically. The examiner inputs the participant’s answers on the android device. The overall score ranges from 0 to 25.

The social situations were inspired from The Faux Pas test (62), Sally and Anne test in its original (63), the revised version suggested by Riviere in a personal communication (62) and the strange stories of (64).

ο Facial Emotions Tunisian Test for Children (FETTC) (62):

The test consists of a combination of a static and a dynamic subtest. The static subtest includes 114 photographs of actors mimicking six basic emotions (happiness, disgust, fear, surprise, sadness, and anger) and neutral expression with three levels of intensity of facial emotions for the six basic emotions: low, medium, and high. The dynamic subtest includes 36 videos with actors mimicking six basic emotions. Participants are asked to view each face and to identify and select the facial emotion that corresponds to each photo or video.

During the task, each proposed facial expression with the proposals remains on the screen for 15 s. After this time and when the participant was not able to select his choice, the next stimuli were presented. Once a response is chosen for a given face, the participant is not able to revise it, and the next proposal of facial emotion is presented.

#### Neurocognition

2.4.3.

The following table summarizes the tests used to assess the different cognitive functions (Table 2).

**Table 2 tab2:** Tests used to assess neurocognition.

Cognitive function to be assessed	Test	Comments
Intellectual efficiencies	Raven’s Progressive Matrices (SPM)	It assesses general non-verbal mental abilities and deductive reasoning/A non-verbal estimate of fluid intelligence (63)
Processing speed	Wechsler Adult Intelligence Scale III (WAIS III)/Wechsler Intelligence Scale for Children (WISC-5)	The test includes 15 subtests that provide an extensive assessment of both verbal and non-verbal abilities. The Processing Speed Index (PSI) included Digit Symbol-Coding (DSC) and Symbol Search (64)
Working memory and selective attention	The digit-span task	Digit Span Forward+ Digit Span Backwards (65)
	Baddeley’s double task	It includes three steps: Single-task condition/Tracking-Single-task condition/Dual-task condition (66)
Episodic memory	Grober and Buschke’s task	Adapted to the Tunisian population in 1998. It encompasses several phases: a control-encoding task, three free recalls for all items and three cued recalls for items not retrieved at free recall, a recognition phase, and a delayed free/cued recall phase (after 20 min) (67).
Executive functions	Trail Making Test A and B (TMT A and TMT B)	TMT A evaluates attention. TMT B evaluates inhibition, mental flexibility, and working memory (68).
	STROOP test	It measures the ability to inhibit cognitive interference (the Stroop Effect), selective attention capacity and skills, and processing speed (69, 70).
Visuo-constructional ability	Rey Complex Figure (RCF)	It is used for the assessment of visuo-constructional ability, planning, and visual memory (71).
Cognitive flexibility	Verbal and semantic Fluences Tests	We will use the Arabic version. It consists of 3 parts: The phonemic fluency task (using the initials “ق” then “ب”), the semantic fluency (animals then fruits), and the alternate verbal fluency (by alternating a word belonging to the clothing category with a word beginning with the letter “ل”) (72, 73).

#### Pragmatic skills

2.4.4.

The Children’s Communication Checklist (CCC-2) Bishop (74), will be used to identify and evaluate pragmatic language impairment in this population. It is a parent or caregiver-rated questionnaire that quantifies the strengths and weaknesses of children’s communication from 0 (“less than once a week”) to 3 (“several times a day”). It includes 70 items on 10 pragmatically constructed subscales: Speech, Syntax, Semantics, Inappropriate Initiation, Coherence, Use of Context, Non-verbal communication, Social Behavior, Stereotyped language, and Interests (75). The CCC reports a sensitivity value of 0.89 and a specificity value of 0.97 for identifying children with autistic symptomatology and pragmatic social impairment (76).

#### Social skills

2.4.5.

The Social Responsiveness Scale (SRS) (77) is a validated questionnaire for assessing the ability to engage in emotionally appropriate reciprocal social interactions, communication, and stereotypies in autism. The scale is filled out by parents and measures the degree of social impairment in participants. Five subscales are distinguished: awareness of the relational environment, social cognition, social communication, social motivation, and mannerisms. It comprises 65 items on a 4-point Likert scale generating one total score (max. 195). A coefficient of social reciprocity is calculated by combining these different subscales. High scores are associated with more severe social impairments. The SRS scores correlate strongly with algorithm scores of the ADI-R (78).

#### Self-esteem

2.4.6.

The Rosenberg Self-Esteem Scale (RSES) (79) is a 10-item scale that measures global self-worth or self-acceptance with both positive and negative feelings about the self. All items are answered using a 4-point Likert scale ranging from “strongly agree” to “strongly disagree.” Higher scores indicate higher self-esteem.

#### Study procedure

2.4.7.

The study procedure is represented in the Figure 1.

**Figure 1 fig1:**
[figure not shown]
Study procedure.

## Statistical analysis

3.

Data collection and statistical analysis will be performed using the Statistical Package for Social Sciences (SPSS) version 25.

We will proceed to the comparison of the different scores of each group at the beginning and at the end of the study as well as to the comparison of the progression of the two groups between them at the beginning and at the end of the study.

The primary objective of our study is to facilitate the transfer of new skills to daily life and thus the global functioning of this population. Primary outcomes will be based on the GAF score and The Global Executive Composite score of the BRIEF. All other measures (social cognition, neurocognition, social skills, pragmatic skills and self-esteem) will be secondary outcomes and will be assessed descriptively.

For the descriptive statistics, we will calculate means and standard deviations for age and educational level and for categorical data, e.g., sex we will use Fisher’s Exact Chi-squared test.

For each neurocognitive and social cognition domain measure, we will conduct *t*-tests for independent samples to examine baseline differences for this sample. To examine Group X Time interaction for measuring treatment effects, we will conduct a Repeated Measure-Analysis of Variance (RM-ANOVA) that compared the difference scores of NEAR-group vs. Control-group at baseline and at the completion of the intervention.

A RM-ANOVA will also be used to examine differences in pragmatic skills, social skills and self-esteem.

For the two measures where there were statistically significant baseline differences, we will repeat the RM-ANOVA using baseline cognitive scores as a co-variate to control for baseline differences.

The significance level for all statistical analyses will be set to *p* = <0.05.

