## Discussion

5.

The NEAR program is tailored to the participant’s age and interests. It will address the adolescent’s behavior, cognitive and communication skills and offer regular reinforcement of positive actions. Also, parents as well as other family members, will be involved in the treatment program (through home tasks) so that it becomes part of the adolescent’s daily life.

At the end of our study, we expect to see an improvement in terms of social functioning and social skills in this population and so a better social integration and quality of life. Thus, this adaptative program could be a promising socio-cognitive intervention that creates new perspective for adolescents with ASD. In fact, the social demands of adolescence present a particularly difficult developmental stage and a continuous challenge throughout the life span, particularly for people with ASD. Despite their social impairments, maintaining and sustaining friendships remained the greatest challenge for adolescents with ASD and they often express concerns about their lack of reciprocal friendships (80).

Also, we expect neuropsychological improvements, mainly in theory of mind (ToM), which is one of the most frequent and disabling cognitive impairment in autism (28, 81). This improvement could be helped by the enrichment added in bridging groups with scenarios of problematic social situations in autism. This will promote the development of social coping skills, as well as to work through behavior management strategies. In fact, social stories can be effective for individuals with ASD and provide a framework for understanding and addressing ToM deficits characteristic of these individuals (82–84). The choice of group role-plays is motivated by the results of many studies that discuss the use of this method to develop social and pragmatic skills of autistic children (85, 86). Furthermore, “Feelings” game will be used to enhance empathy in our population. It uses two game mechanics to generate empathy: naming which emotion is felt in a particular situation (Introspection) and guessing which feeling other people feel in the same situation (decentering) (56). It is important to highlight that people with autism have a deficit of cognitive empathy but a surfeit of emotional empathy (87).

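### Two primary outcomes each get their own 0.05 with no success rule, and the informant for the BRIEF primary score is left open

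*Protocol article*

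**What the plan says.** The Statistical analysis section (section 3) names the primaries: "Primary outcomes will be based on the GAF score and The Global Executive Composite score of the BRIEF". It closes with one rule on alpha: "The significance level for all statistical analyses will be set to *p* = <0.05". All other measures "will be secondary outcomes and will be assessed descriptively", so the confirmatory family is the pair of primaries. The treatment effect is described this way: "To examine Group X Time interaction for measuring treatment effects, we will conduct a Repeated Measure-Analysis of Variance (RM-ANOVA"), comparing the groups at baseline and at completion.

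On the BRIEF, the Global functioning section (2.4.1) says: "Executive function behaviors in the school and home environments will be assessed using the BRIEF". It adds: "This questionnaire is elaborated for parents and teachers of school-age children". Both sections refer to one Global Executive Composite. Neither says whose rating supplies it, or how two ratings would be combined.

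**The concern.** A stated level of 0.05 for all analyses, applied to two primary outcomes, gives each its own 0.05. Nothing in the text stops the trial from being called positive on whichever of the two falls below the threshold. In that case the error rate for the primary claim is above the level that the plan names.

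The open informant adds a second degree of freedom. The instrument is meant for parents and teachers and is to cover home and school. A reader therefore cannot tell which rating becomes the primary composite, and the choice could be made after the data are seen. What is at stake is whether a positive primary result can be read at its nominal level.

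**Working it through.** **Inputs from the protocol article**
- Alpha per test: 0.05 (section 3).
- Primary outcomes: 2 (section 3).
- Group size: 30 patients in all. The NEAR group is three groups of five, so 15. The control group is 30 − 15 = 15 by inference (section 2.3).
- Test: Group × Time with two time points, which equals a two-sided t-test on change scores with 15 + 15 − 2 = 28 degrees of freedom. Section 3 does not tie this test to the primaries by name; I take it as the test of the treatment effect.

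**Assumed:** the correlation r between the two outcomes' change scores. The article gives none, so I show a range.

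The plan gives no family-wise level and no power calculation, so it has no figure of its own to reproduce.

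**Step 1. Independent outcomes, success on either.**
1 − (1 − 0.05)² = 1 − 0.9025 = 0.0975, which is 1.95 times 0.05.

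**Step 2. Correlated outcomes, success on either.**
1 − P(|Z₁| < 1.96 and |Z₂| < 1.96), with (Z₁, Z₂) bivariate normal:

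| r (assumed) | Family-wise error |
|---|---|
| 0 | 0.0975 |
| 0.3 | 0.0951 |
| 0.5 | 0.0907 |
| 0.7 | 0.0835 |
| 0.8 | 0.0781 |
| 0.9 | 0.0704 |

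A simulation of t-tests with 15 per group (200,000 replicates) agrees: 0.097, 0.095, 0.092 and 0.077 at r = 0, 0.3, 0.5 and 0.8.

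**Step 3. Success only if both are significant.**
The chance that both tests reject falsely cannot exceed the chance that one does, so the error is at most 0.05. The inflation in steps 1 and 2 therefore depends on an either-outcome claim.

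**Step 4. After correction.**
Holm compares the smaller p-value with 0.05/2 = 0.025 and, if that is significant, the larger with 0.05. With both null hypotheses true, a false claim needs at least one p-value below 0.025. For independent outcomes that has probability 1 − 0.975² = 0.0494. For any correlation it is at most 2 × 0.025 = 0.05.

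**Step 5. Cost at 15 per group** (two-sided t-test, 28 df, effects in SD of the change score).
- Effect detectable with 80% power: 1.06 SD at 0.05 (critical t 2.048) and 1.18 SD at 0.025 (critical t 2.368). The squared ratio, (1.179/1.060)² = 1.24, is equivalent to about 24% more patients.
- Power at an assumed 1.0 SD: 0.75 at 0.05 and 0.65 at 0.025.
- Power at an assumed 0.8 SD: 0.56 at 0.05 and 0.44 at 0.025.

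These are losses at the first Holm step. Once one outcome is significant, the other is tested at 0.05.

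**The case against.** **The rule may be in an analysis plan.** A success rule and a multiplicity procedure are often left to the SAP, which is not shown, and a general 0.05 statement is compatible with a both-must-succeed rule there. This stands in part: the article never says that either outcome alone suffices, so the inflation is conditional. It does not remove the point. The article is not silent on alpha. It fixes 0.05 for every analysis, and following that text gives each primary its own 0.05.

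**Three primary scores.** A reader might infer that the parent and teacher ratings make three primary scores, which for independent scores would give 1 − 0.95³ = 14.3%. The article does not support this. It speaks of one composite and never says that two will be tested. Two ratings of the same adolescent would also hardly be independent. What the text supports is that the informant is not named.

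**Parent ratings as the biased choice.** A reader might infer that the teacher rating must be primary, because the Discussion says that "parents as well as other family members, will be involved in the treatment program" and the trial is open. Parental involvement is a fair reason to settle the informant with care. But the article does not say that teachers are blind, or that the GAF rater is, and it calls the GAF rating subjective. Nor does it show that teacher ratings exist at baseline. Requiring the teacher rating would also take the home setting out of a primary outcome meant to reflect daily life.

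**Materiality.** Section 2.3 allocates patients by motivation and availability, and this may produce false claims more readily than multiplicity does. That is fair. The percentages above are nominal test-level figures for comparable groups, not the overall chance of a wrong conclusion in this trial.

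**Conclusion.** The point holds in conditional form. As written, two primary outcomes are each tested at 0.05 with no split, order or success rule. If significance on either is taken as success, the nominal family-wise error is between about 7% (r = 0.9) and 9.75% (r = 0), against a stated 5%. So a doubling is approached only at low correlation. The correlations are assumed, and the figures leave out bias from the open, non-randomized design. If both outcomes were required, there would be no inflation, but the article does not say so. Separately, the informant for the BRIEF composite is undefined. That is an ambiguity in a primary outcome, not evidence of an additional primary test.

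**What to change.** In section 3, state that GAF and the BRIEF Global Executive Composite at T2 form the primary family and are tested with the Holm procedure at an overall two-sided 0.05. Alternatively, name one of them as the single primary and make the other secondary; this needs no alpha split.

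Also state which informant's composite is primary and report the other as secondary. Fix this before the final analysis and without regard to results. The Trial status section reports 26 of the planned 30 recruited, with 15 adolescents already in the NEAR programme. The choice should therefore be dated, and made only among ratings that were collected from baseline onward.

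No new data or patients are needed. The cost of Holm is the stricter first threshold and the loss of power in step 5 of the working, which is moderate for a trial of 30. The cost of a single primary is that the other outcome can no longer carry the main claim.

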## Ethical considerations

4.

ο Informed consent of the parent has been obtained.ο Information form will contain: Justification for research, the outline of the study, risks, confidentiality, and voluntary participation telling patients about the freedom to withdraw from the study whenever they wish to (without any change in their usual treatment).ο Confidentiality indicates how the personal information obtained from the patient will be kept secret (Data safety).ο Ethical committee approval has been obtained.

## Discussion

5.

The NEAR program is tailored to the participant’s age and interests. It will address the adolescent’s behavior, cognitive and communication skills and offer regular reinforcement of positive actions. Also, parents as well as other family members, will be involved in the treatment program (through home tasks) so that it becomes part of the adolescent’s daily life.

At the end of our study, we expect to see an improvement in terms of social functioning and social skills in this population and so a better social integration and quality of life. Thus, this adaptative program could be a promising socio-cognitive intervention that creates new perspective for adolescents with ASD. In fact, the social demands of adolescence present a particularly difficult developmental stage and a continuous challenge throughout the life span, particularly for people with ASD. Despite their social impairments, maintaining and sustaining friendships remained the greatest challenge for adolescents with ASD and they often express concerns about their lack of reciprocal friendships (80).

Also, we expect neuropsychological improvements, mainly in theory of mind (ToM), which is one of the most frequent and disabling cognitive impairment in autism (28, 81). This improvement could be helped by the enrichment added in bridging groups with scenarios of problematic social situations in autism. This will promote the development of social coping skills, as well as to work through behavior management strategies. In fact, social stories can be effective for individuals with ASD and provide a framework for understanding and addressing ToM deficits characteristic of these individuals (82–84). The choice of group role-plays is motivated by the results of many studies that discuss the use of this method to develop social and pragmatic skills of autistic children (85, 86). Furthermore, “Feelings” game will be used to enhance empathy in our population. It uses two game mechanics to generate empathy: naming which emotion is felt in a particular situation (Introspection) and guessing which feeling other people feel in the same situation (decentering) (56). It is important to highlight that people with autism have a deficit of cognitive empathy but a surfeit of emotional empathy (87).

In this study, the experimental group will benefit from cognitive remediation with NEAR, which combines cognitive remediation and social rehabilitation. This program targets a wide range of neuropsychological deficits (attention, visual field, verbal and visual short-term memory, working and long-term memory, planning, problem-solving, inhibition, mental flexibility…) with an expectation that the improvement after program will translate into greater competency in daily life (47, 88).

NEAR method focuses also on adhering to principles of motivation and learning. The impact of motivational factors on the development of social skills and social cognition in ASD are thought to have downstream effects on the development of social cognition (11). Moreover, this method represents an attractive therapeutic tool for young subjects. In a pilot study testing the NEAR program with four preadolescents and adolescents aged 11–15 years with either ADHD or ASD, all participants enjoyed the program. Also, they found it a fun and effective way to learn new strategies, and they found a pleasure of seeing each other again every week. They perceived support and the development of self-help skills (55). NEAR method also integrates the metacognitive dimension that helps the participants to develop the capacity to reflect on their own cognitive processes. Some studies suggest that metacognitive aspects are of particular importance for social abilities in children and adolescents with ASD (89). The sharing time during the Bridging group (difficulties encountered during the exercises, strategies used, link with daily life, …) aims to foster self-esteem, reinforce intrinsic motivation but also to improve their autonomy, social functioning of the participants, and improve pragmatic skills.

From this same perspective, the impact of cognitive remediation on functional outcomes appeared to be significantly greater in studies that also included psychiatric rehabilitation, suggesting that these two therapeutic approaches may act synergistically (90, 91).

Taking into account the particularities of this population, some difficulties may be encountered by the therapist and arise in performing this study. The reasons relate to some of the characteristics of ASD. The first issue is that in a group situation, the clinician may struggle to accommodate their unique learning styles and needs. In fact, the heterogeneity of symptoms, the presence of behavioral disorders, the lack of reciprocity and autonomy represent a challenge for workers in medico-social institutions (92, 93). Additional limitation that the therapist may face during the bridging group is the characteristics of autistic speech which may differ significantly from one person to another: participants may say things that have no meaning or that do not relate to the conversations they are having with others (off-topic subject), they may repeat words he or she has heard (Immediate echolalia and delayed echolalia), they may ask rhetorical questions, they may have difficulties in understanding idiomatic expressions and metaphors… Therefore, the duration of the sessions will vary according to the capacities of the participants and the exchanges between them and the therapist has to adjust to the different situations encountered.

Moreover, adolescents with ASD, having narrow interests can widely interfere with the different activities of this adapted program. This lasting, intense interest is a common behavior in children with Autism, according to the National Institute of Health (NIH) (up to 88%) (94). In these cases, instead of attempting to prevent or continuously redirect the participant from talking about a preferred interest, the therapist will try incorporating this interest to help the candidate engage in conversation with others and so encourage him to become more socially engaged with the rest of the group. Once the conversation is going, this can be a great opportunity for the therapist to help them learn to take another person’s point of view that would create a positive organizational climate in the group.

Besides, anxiety and autism are often closely intertwined, this comorbidity is linked with significant functional impairment, and it can be related to a neurological response. Specific overlapping areas of the brain are likely involved in both the manifestation of autism and anxiety. For example, neural responses in the brain related to how a person processes rewards can be a risk factor for anxiety and a risk factor for autism (95). This anxiety may be manifested in intolerance and fear of change and uncertainty during the sessions and frustration at difficulty or failure in computerized cognitive exercises and so a quick change of exercises which can affect the effectiveness of the cognitive training. Finally, pharmacological therapy could have an effect on cognition and the chance to NEAR program response.

